#### Control group (standard care as usual)

Patients in the control group will receive standard care as usual, as determined by the healthcare system in the participating countries. The dose and frequency of usual care will be deemed appropriate by the medical practitioner in charge of their treatment.

#### Criteria for discontinuing or modifying allocated interventions

When a patient or family caregiver dies during the study period, a bereavement protocol will be in place. The national trial manager will be notified about the death of a participant by either the intervention nurse (for the FOCUS+ intervention) or the data collector (for the FOCUS+ and iFOCUS intervention) who should be informed about this when trying to make an appointment with the dyad. The bereaved participant from the iFOCUS intervention will be able to inform the national trial manager about the passing of their relative via e-mail. For the FOCUS+ intervention, the bereaved participant will receive a phone call from the intervention nurse outlining condolences and the options for where they can access support (relevant to each country) if required and what the implications are for the study. For the iFOCUS intervention, the bereaved participant will receive a similar phone call from a research assistant appointed within each research team, that has relevant qualifications and/or significant clinical experience (e.g. a psychologist). If the bereaved person seems very distressed, the nurse or research assistant can offer to call the person a second time (e.g., 1 week later) to determine whether the person has made contact with a source of support (e.g., family, clergy, physician, bereavement group). Bereaved persons will not be asked or expected to complete follow-up study questionnaires but will be offered the option to continue to fill out an abbreviated package of follow-up questionnaires that are relevant to the remaining partner (e.g. emotional functioning and QoL scale). Any other reason for discontinuing the interventions is described in the informed consent (dyads can withdraw from the study at any moment) or under the section of adverse events (such as psychological distress).

#### Strategies to improve adherence to the intervention protocols

Strategies include:Nurses delivering the intervention will receive extensive training and additional continuous follow-up training to provide them with the knowledge and skills required to successfully implement the intervention.The FOCUS+ intervention is comprehensively manualized. Nurses will be trained in the use of an intervention manual to deliver the FOCUS+ intervention.Adherence and fidelity monitoring: nurses delivering the FOCUS+ intervention will be required to self-assess fidelity based on the recordings of the initial delivery of the three FOCUS+ sessions with dyads with whom they have carried out the intervention. These fidelity checks will be conducted in the early phases of delivery, to allow for intervention nurses to reflect on the initial experience of delivery. Following this early phase, intervention nurses will be provided with routine reports on overall fidelity checks to allow them to adapt their practice if needed to ensure appropriate levels of fidelity are met throughout delivery.It is proposed that 20% of dyads are assessed for objective fidelity using the intervention fidelity checklist by a member of the research team, with the dyad’s full intervention participation (that is all sessions of the intervention) assessed as one check.Discussing fidelity of FOCUS+: planned and unplanned adaptations in the interventions during the training of the nurses, the regular community of practice sessions with trainers and nurses, and the monthly follow-up sessions between the trainers and nurses (virtual meetings during the study period).A number of aspects of adherence are built into the iFOCUS web-module; e.g. during web-sessions dyads are asked to confirm that both of them are present and indicate where they are sitting at the computer.If dyads do not fully complete an iFOCUS web-session and exit the session before finishing, a reminder will be sent via email.Dyads who experience problems with onboarding for the web-sessions will receive help from the national trial manager with onboarding via a phone call.Routine monitoring will also include surveys of satisfaction with the interventions.

#### Relevant concomitant care and interventions that are permitted or prohibited during the trial

There are no restrictions regarding concomitant care during the trial outside of the three trial arms.

### Outcomes

#### Study endpoints and assessments

This study uses both qualitative and quantitative data to measure the outcomes of the intervention. Data will be collected three times from patient-caregiver dyads; (1) baseline measure before randomization to the study arms (T_0_) (2) first follow-up at 12 weeks (T_1_) and (3) second follow-up at 24 weeks (T_2_).

The primary endpoints are emotional functioning and self-efficacy of both the person with advanced cancer and the family caregiver at T_1_. The secondary endpoints are QoL of the patient and caregiver, benefits of illness, coping, dyadic communication, ways of giving support at T_1_. All listed primary and secondary outcomes are measured at T_2_ and formal healthcare use and costs are measured at T_1_ and T_2_.

Validated questionnaires will be used to measure the primary and secondary endpoints. In addition, data on socio-demographic characteristics, care received and participant perspectives on the acceptability, feasibility, and usefulness of the intervention will be collected. An overview of the instruments, the underlying measured concepts, and their timing can be found in Table 4. The complete questionnaire is added as a supplementary file.

**Table 4 Tab4:** Instruments, underlying concepts, and timing

Concept	Measured by^b^	Timing^**a**^		
		T_0_ (Before randomization)	T_1_ (T_0_ + 12 weeks)	T_2_ (T_0_ + 24 weeks)
***Outcome measures used for the primary endpoints***				
**Emotional Functioning**	EORTC [14–16] 10 emotional functioning items described by Jabbarian et al. [15]. For **patients** (10 items): For **caregivers** (10 items):	✓	✓	✓
**Self-efficacy**	The Lewis´ Cancer self-efficacy scale [17] (validated by Northouse [5]) For **patients** (17 items) For **caregivers** (17 items)	✓	✓	✓
***Outcome measures used for the secondary endpoints***				
**Quality of life** (also covers additional secondary outcomes such as hopelessness, anxiety, depression, etc.)	For **patients** (23 items): - EORTC QLQ-C15-PAL [18] plustwo social functioning items (#26, 27) + one item about overall health (#29) from EORTC QLQ-C30 [19] - Social well-being scale from FACT-G [20] For **caregivers** (35 items): - The Caregiver Quality of Life Index-Cancer (CQOLC) [21]	✓	✓	✓
**Benefits of illness**	Benefits of illness scale [22] For **patients** (5 items) For **caregivers** (5 items)	✓	✓	✓
**Coping**	A shortened version of Brief Cope [23] (#1–3,5-10,13-16,19-21,23–26) For **patients** (20 items) For **caregivers** (20 items)	✓	✓	✓
**Dyad communication**	The five items ‘Active engagement scale’ from the ´Ways of giving support questionnaire´ [24]. Three scales (10 items) from the ‘Dyadic Coping Inventory’ [25]: ‘Stress communication by oneself’, ‘Stress communication by partner’ and ‘Evaluation of dyadic coping’. For **patients** (15 items) For **caregivers** (15 items)	✓	✓	✓
**Health economic measures**	EQ5D5L [26] and CSRI [27] For **patients** (23 items) For **caregivers** (14 items)	✓	✓	✓
***Background characteristics***				
**Socio demographics, illness-related factors, social factors**	A mix of socio-demographic items from different studies (self-constructed): - Sex, age, relationship status, living situation, having children, educational level, employment status, total monthly net income, financial difficulties related to physical condition or medical treatment, private medical insurance, religion, member of a minority ethnic group, dyad’s relationship For **patients** (14 items) For **caregivers** (15 items)	✓		
***Other aspects evaluated***				
**Items about computer skills**	Three FOCUS items about computer skills (self-constructed) For **patients** (2 items) For **caregivers** (2 items)	✓		
**Process evaluation**	FOCUS items asking about **experience** and **satisfaction** with the intervention. (self-constructed) For **patients** (12 items) For **caregivers** (12 items)		✓	
**Process evaluation**	**Experiences with the intervention**: (self-constructed) - Interviews with patients and family caregivers - Interviews with nurses delivering the intervention		✓	
	**Fidelity: FOCUS+** (self-constructed) Session characteristics (e.g. length, timing), random sample intervention checklists, random sample audio-taped intervention sessions		✓	
	**Fidelity: iFOCUS** (self-constructed) Data from web-based program (e.g. number of sessions logged into, time taken to complete session)		✓	
	**Routine data on recruitment** (self-constructed) (e.g. potential participants, initial engagement, eligible participants, enrolment)	✓		

^a^For T_1_, questionnaires can be filled in between T_0_ + 12 weeks minimum and T_0_ + 16 weeks maximum. For T_2_, questionnaires can be filled in between T_0_ + 24 weeks minimum and T_0_ + 28 weeks maximum

^b^All measures were validated in each of the participating countries

### Participant timeline

The face-to-face FOCUS+ intervention is a home-based intervention consisting of two 90-min home visits and one 30-min online video session, conducted by a trained intervention nurse who visits the dyads at home over 12 weeks, with 4 weeks between each session. The web-based iFOCUS intervention is a self-managed intervention that is completed autonomously by the patient-caregiver dyads at home. The iFOCUS intervention encompasses four sessions for the dyads (with 3 weeks between each session) over 12 weeks. Data will be collected three times from patient-caregiver dyads: 1) baseline measure (T_0_) after which the dyad will immediately be randomized to one of the study arms, 2) first follow-up at 12 weeks after the baseline (T_1_), and 3) second follow-up at 24 weeks after baseline (T_2_). Figure 2 provides a flowchart of the participant timeline and the data collection.

**Fig. 2 Fig2:**
[figure not shown]
Participant timeline

### Sample size calculation

We consider the demonstration of an intervention effect (for each of both interventions) on at least one of the primary endpoints for either the patient or the caregiver as a success. A pre-determined strict fixed sequence (FS) procedure defines the prospectively hierarchical ordering of the endpoints, for this study the hierarchical order is emotional functioning (1) and self-efficacy (2). Testing of null hypotheses proceeds according to their hierarchical order, that is, H(1)0 is tested first at a significance level of 5%, and if H*(*1*)*0 is rejected then H*(*2*)*0 is tested at the same significance level, otherwise H*(*2*)*0 is not tested at all. The strict FS approach has the highest power for testing the first hypothesis (outcome: emotional functioning) compared to the other methods, as it does not save any portion of alpha for testing later hypotheses [10]. The reference mean value for emotional functioning from EORTC for all cancer patients, stage III-IV is 71.5 (SD: 23.8) [28]. Alpha is set at 0.0125 instead of 0.05 to account for multiplicity (2 comparisons with control group * 2 participant groups [patients and caregivers]). We set 1-beta (i.e. statistical power) at 0.9. The expected difference between the control group and the intervention arms in the primary outcomes is 0.375 SD at T1 (12 weeks).

With these parameters *n* = 203 is needed in each arm across all countries (i.e. 609 in total). Anticipating a 65% retention rate at T1, which is more conservative than found in previous studies in the USA on the FOCUS interventions [5–7] due to the advanced cancer population included in this study, 938 dyads must be enrolled across the 6 countries (313 per group). This means that 156 dyads (i.e. 52 in each of the 3 arms) need to be enrolled in each country. Based on previous studies in the US [5–7] we expect an enrolment rate of 55% of those dyads referred to the study, meaning that about 282 dyads will need to be screened and identified in each country. The feasibility of recruitment has been evaluated based on previous research and discussions with clinicians in eligible hospitals.

### Recruitment

Staff in each department in the participating hospitals will screen for patients meeting the eligibility criteria. After eligible patients are identified, the study is orally presented to the patient-caregiver dyad and they are invited to participate in the study by a research assistant. This research assistant will explain the study and refer the patient and their family caregiver to the contact person of the research team. A data collector will make an appointment with the dyad at home (or preferred location of the dyad) to obtain informed consent.

The recruitment period will last a total of 12 months. Screening will continue until the target population is achieved. Based on conservative estimations of the number of eligible dyads that could be enrolled, obtaining the numbers required by the power calculations is realistic.

## Assignment of interventions

### Allocation

Randomization will be performed per a computer randomization schedule with a 1:1:1 allocation ratio to one of the two intervention arms or the standard care arm (control group) using simple randomization. Participants will be randomized using the Mersenne Twister Random Number Generator, which is an online, central randomization service [29]. Each dyad will be randomized to one of the three study arms. Recruitments for the study within a country will continue until at least 52 dyads were randomized.

Allocation concealment will be ensured, as the randomization service will not release the randomization code until the patient has been recruited into the trial, which takes place after all baseline measurements have been completed.

All dyads who fulfil the inclusion criteria, who give consent for participation, and complete the baseline measurements (obtained by the data collector) will be randomized. Randomization will be immediately requested after completion of the baseline questionnaires from the online service Mersenne Twister Random Number Generator by the data collector, who is then able to inform the dyads of their allocation to one of the study arms. Randomization will thus be conducted without any influence of the principal investigators, raters, or clinicians. Research staff responsible for the data analyses of the trial will not be allowed to receive any information about the group allocation.

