All identified secondary endpoints (Quality of Life [including separate items of hopelessness, anxiety, depression], benefits of illness, coping, dyad communication, all at T1) will be evaluated by testing the FOCUS+ and iFOCUS against care as usual (control group) for each participant population (patients/caregivers) separately. In total, 4 comparisons are performed for each outcome variable. For each secondary outcome variable, a mixed model is applied with the T1 measurement value as the outcome variable, recruitment center as random effect, and randomization group and baseline measurement of the variable (T0) as predictor variables. We will perform analyses on both ‘intention-to-treat’ and per-protocol principles, applying the same principles as described above.

By including the baseline measurement as a predictor variable (ANCOVA), preexisting differences will be controlled, enhancing the sensitivity of the analyses. To interpret the magnitude of the effects for the different outcomes, we will estimate effect sizes (Cohen’s d). All statistical tests will be two-sided and considered significant if *p* < 0.0125.

All primary outcomes and secondary outcomes as listed above will also be analysed at T2 (6 months) to evaluate longer-term effects, using the same analysis procedures.

The cost-effectiveness of the interventions will be determined by analyzing patterns and costs of healthcare utilization and effects on quality of life. Costs will be estimated by combining the reported frequency of health care use by participants with country-specific unit costs for each service domain. Quality of life will be measured by combining EQ5D5L with country-specific preference weights. We will evaluate the robustness and consistency of results in population-specific outcome measures EORTC, FACT-G and CQOLC. Data will also be collected on the types and amounts of informal care provided to patients in each arm of the study, to investigate if the amount or patterns of informal care change as a result of the intervention. The outputs will be mean costs of care for patients in each arm of the study, cost per year of life gained (if survival is affected significantly by the intervention and the costs in the intervention groups overall are higher), and (if appropriate) the additional costs of achieving a better quality of life outcomes (including estimates of cost per quality-adjusted life-year gained).(3)Exploratory hypotheses testing

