For all exploratory endpoints, two-sided statistical tests will be considered significant if *p* < 0.05.

For the outcomes that are measured identically for the patient and the caregiver, we will assess the effect on the dyad as a whole (i.e. both patient and family caregiver). For the outcome instruments that led to comparable estimated differences between FOCUS+ and standard care and iFOCUS and standard care, the effect will be assessed on the dyad as a whole by adding an extra level (dyad) to the linear regression model.For each of the primary and secondary endpoints, subgroup analyses will be performed using formal interaction tests to explore the extent to which the outcomes of the trial differ by country, gender, and socioeconomic status. Interaction terms between respectively country, gender, and socioeconomic status on the one hand and the trial arms on the other hand will be added to the analysis models. For the country variation multilevel mixed model analyses will also be performed to additionally account for potential clustering by country (i.e. participants nested within a country). Outcomes will be analysed with country as random factor.(4)Other analysesBackground reports describing care as usual for people with advanced cancer will facilitate the understanding of the results of the between-country comparisons.Process evaluation of the implementation of the interventions will be analyzed following the MRC framework for evaluating complex interventions [30], integrating normalization process theory (NPT) [31] and the RE-AIM framework [32]. Data analysis for the process evaluation will include a) standard statistical descriptions of the quantitative data from the intervention checklist and routine monitoring to describe adherence to the implementation. This analysis will determine cut-off points for good intervention adherence and, hence, inform the per-protocol analyses; b) analyses of the qualitative data (semi-structured interviews with patients and their family caregiver and post-intervention interviews with the nurses who delivered the face-to-face FOCUS+ intervention) will be performed (see below - Qualitative analysis).

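### With 156 dyads per country, simple randomization makes the stated 52 per arm very unlikely, and the country stopping rule does not match the 156

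*Protocol article*

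**What the plan says.** The Sample size calculation section derives a trial-wide requirement of 203 evaluable dyads per arm, inflates it for 65% retention and divides by six countries: "This means that 156 dyads (i.e. 52 in each of the 3 arms) need to be enrolled in each country".

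The Allocation section describes the method: "Randomization will be performed per a computer randomization schedule with a 1:1:1 allocation ratio", carried out "using simple randomization" through a central online service, with the dyad as the unit. It names no stratification factor, block or minimization scheme. It then gives a country-level rule: "Recruitments for the study within a country will continue until at least 52 dyads were randomized".

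Country matters to the aims. Effectiveness in different healthcare systems is among the project objectives, and the exploratory analyses use interaction tests to "explore the extent to which the outcomes of the trial differ by country, gender, and socioeconomic status". The primary model has recruitment center as a random effect. Country enters only the exploratory models.

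**The concern.** The sample size section words 52 per arm per country as something that has to be enrolled. Independent 1:1:1 draws do not control arm sizes within a country, so that number is an average and not a property of the design. The recruitment rule beside it uses the same figure of 52, but attaches it to dyads in a country and not to dyads in an arm, so the two sections do not agree on when a country is finished.

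At stake is the balance of arms within countries, in a trial whose six-country setup is presented as a basis for comparing healthcare systems. So is a clear enrollment target. The allocation method is fixed in this document and cannot be repaired in an analysis plan.

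**Working it through.** **Inputs.** From Sample size calculation: α = 0.0125, power 0.90, difference 0.375 SD, retention 65%, 156 dyads per country, six countries, 55% enrollment of referred dyads. From Allocation: 1:1:1 simple randomization. Two-sided testing is stated under the secondary analyses ("All statistical tests will be two-sided and considered significant if *p* < 0.0125"). I assume that every country enrolls exactly 156.

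**1. The plan's own figure.** n per arm = 2(z₁₋α/₂ + z₁₋β)²/d² = 2(2.4977 + 1.2816)²/0.375² = 203.1. The stated 203 is reproduced (204 if rounded up, 205 with the noncentral t). Inflation: 203/0.65 = 312.3, so 313 per arm; 609/0.65 = 936.9, against 938 stated. Then 938/6 = 156.3, so 156 per country, and 156/3 = 52. The 936 in the abstract is 6 × 156; the gap from 938 is rounding. So 52 is the trial-wide requirement, inflated for retention and shared out over countries and arms.

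**2. Arm counts in one country.** Each count is binomial(156, 1/3): mean 52, SD = √(156 × 1/3 × 2/3) = 5.9, 95% range 41 to 64. The exact split has probability 156!/(52!³ × 3¹⁵⁶) = 0.0053. In 400,000 simulated six-country trials:
- the smallest arm in a country averaged 45.9;
- the gap between largest and smallest arm had median 11 and 95th percentile 24;
- the smallest of the 18 country-arm cells had median 42 (95% range 35 to 46).

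**3. The stopping rule, read both ways.**
- As a country total: 6 × 52 = 312 dyads, 104 per arm, 104 × 0.65 = 67.6 evaluable per arm, power about 38%. This contradicts 156 per country.
- As per arm: simple randomization until every arm holds 52 needs on average 174.5 dyads per country (95th percentile 196). That is 174.5 × 6 = 1,047 in total against 936, about 12% more. At 55% enrollment it means 174.5/0.55 ≈ 317 referred dyads per country, against the stated 282.

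**4. Primary power.** Trial-wide arm size: mean 312, SD = √(936 × 2/9) = 14.4, 95% range 284 to 340. For arms of size a and b, power = Φ(0.375/√(1/(0.65a) + 1/(0.65b)) − 2.4977). Balanced arms give 89.9%. Over 20,000 simulated trials the mean was 89.9%, the 2.5th percentile 88.3% and the lowest 86.6%.

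**5. A country contrast.** A 41 v 64 split changes its standard error by √((1/41 + 1/64)/(2/52)) = 1.02, a 2% increase.

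**6. Restricted allocation at 156 per country.** Fixed blocks of 3 or of 6 divide 156 and give exactly 52/52/52. Mixed blocks of 3 and 6 gave a smallest arm of 51 or 52 (52 in about 80% of 3,000 runs). Mixed blocks of 6 and 9 never went below 50. Stratifying by country with simple randomization inside each country leaves the 0.5% unchanged.

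**The case against.** The strongest reply is that nothing important depends on 52. The power requirement is 203 per arm across all countries, no power claim attaches to a country-arm cell, and under 1:1:1 allocation 52 is the correct expected count. Simple randomization is valid and fully unpredictable. That has value here, because dyads are not blinded and the data collector who requests each allocation also tells the dyad the result. The primary model already carries recruitment center, and the country interactions are exploratory. All of this stands, and it limits the point to balance and consistency.

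Four stronger readings are tempting and are not supported:
- That the design cannot reach 52 per arm. The stopping rule, if meant per arm, would reach it by recruiting beyond 156.
- That primary inference is at risk. Step 4 shows a mean power loss of about 0.1 percentage points.
- That nearly every trial would have a shortfall in all six countries, taken as a sign of serious harm. At exactly 156 dyads even 51/52/53 counts as a shortfall, so this only restates the 0.5%.
- That FOCUS+ nurses would be overloaded. The article gives two to four nurses per country but no capacity figure to test this against.

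Nor should the stopping rule be taken to show that the trial will stop at 312 dyads. The abstract and the sample size section both give 156 per country, so the sentence is ambiguous and does not set a smaller trial.

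**Conclusion.** The point holds as an inconsistency with a modest design cost. The sample size section presents 52 per arm per country as needed. The allocation method makes it very unlikely with 156 dyads (about 0.5% per country, arm range 41 to 64), and the country stopping rule fits the 156 on neither reading. The effect on the primary comparisons is negligible, and even a marked imbalance costs an individual country contrast only about 2% in standard error. The gain from changing is country-by-arm balance for a comparison that the trial lists among its objectives, and a target that the procedure delivers closely.

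These figures assume 156 dyads in every country, independent draws with probability 1/3, and 65% retention equal across arms. It is a change worth making, not one on which the trial's validity depends.

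**What to change.** Replace simple randomization by restricted allocation within country, run by the same central service. One option is concealed permuted blocks of small, randomly varying size stratified by country, which keep each arm within about 1 to 2 dyads of 52. Another is minimization with a random element, which also balances closely but does not guarantee 52. Naming country as a stratification factor is not enough without blocking or minimization inside it. Add country to the primary model alongside the center random effect.

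No extra dyads are needed. The costs are a reprogrammed allocation list, some predictability in an unblinded trial (limited by stratifying on country and not hospital, and by varying block size), and a formal amendment. The Protocol amendments section requires consortium agreement and ethics approval, and the article lists six committee approvals plus a Danish determination, so the administrative work is real.

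If allocation can no longer be changed, restate 52 per arm per country as an expected number.

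In either case, reconcile the 52 dyads in the Allocation section with the 156 per country in the sample size section. State whether 52 is per arm, and if so, whether a country may recruit beyond 156 to reach it.

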**Methods:**

We will conduct an international multicenter three-arm randomized controlled trial in Belgium, Denmark, Ireland, Italy, The Netherlands, and the United Kingdom. In each country, 156 dyads (936 in total) of people with advanced cancer and their family caregiver will be randomized to one of the study arms: 1) a nurse-led face-to-face intervention (FOCUS+), 2) a web-based intervention (iFOCUS) or 3) a control group (care as usual). The two interventions offer tailored psychoeducational support for patient-family caregiver dyads. The nurse-led face-to-face intervention consists of two home visits and one online video session and the web-based intervention is completed independently by the patient-family caregiver dyad in four online sessions. The interventions are based on the FOCUS intervention, developed in the USA, that addresses five core components: family involvement, optimistic outlook, coping effectiveness, uncertainty reduction, and symptom management. The FOCUS intervention will be adapted to the European context. The primary outcomes are emotional functioning and self-efficacy of the patient and the family caregiver, respectively. The secondary outcomes are quality of life, benefits of illness, coping, dyadic communication, and ways of giving support of the patient and family caregiver.

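### The Allocation section sets each country's recruitment floor at 52 dyads; the sample size needs 156 per country, and 52 is the number per arm

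*Protocol article*

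**What the plan says.** Three places in the protocol article give a per-country number.

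- Abstract, Methods: "In each country, 156 dyads (936 in total").
- Sample size calculation: "This means that 156 dyads (i.e. 52 in each of the 3 arms) need to be enrolled in each country". This follows from 203 evaluable dyads per arm across all countries (609 in total), raised to 938 enrolled (313 per group) for 65% retention at T1.
- Allocation: "Recruitments for the study within a country will continue until at least 52 dyads were randomized". There is no mention of arms in this sentence. The sentence before it says that each dyad goes to one of the three arms, and the method of allocation is given as "using simple randomization" at 1:1:1.

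The Recruitment section adds that screening goes on until the target population is reached, over a recruitment period of 12 months. It repeats no number.

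**The concern.** Read as it stands, the Allocation sentence counts dyads within a country, not within an arm. A national team could take it to mean that its obligation is met at 52 dyads, one third of what the sample size calculation asks of it. It is the only sentence that attaches a number to how long a country keeps recruiting, and six national teams will act on it. At stake is the power of the four primary comparisons on emotional functioning (two interventions against control, in patients and in caregivers).

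**Working it through.** **Inputs, all from the protocol article**

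- Alpha: "Alpha is set at 0.0125 instead of 0.05 to account for multiplicity" (Sample size calculation).
- Sidedness: "All statistical tests will be two-sided" (Quantitative analysis, under the secondary hypotheses). The sample size section names no side, but only the two-sided reading reproduces its figure (step 1).
- Power: "We set 1-beta (i.e. statistical power) at 0.9".
- Effect: "The expected difference between the control group and the intervention arms in the primary outcomes is 0.375 SD at T1 (12 weeks"). The SD of 23.8 cancels because the effect is in SD units.
- Retention at T1: 65%. Allocation 1:1:1, six countries.

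**Step 1. Reproduce the plan's figure.** For two means, n per arm = 2(z₁ + z₂)² / d², with z₁ = 2.498 (two-sided 0.0125), z₂ = 1.282 (power 0.90) and d = 0.375. This gives 2 × (3.779)² / 0.1406 = 203.1, so 203 to 204 against the stated 203; a t-test calculation gives 205. One-sided 0.0125 would give 177 and two-sided 0.05 would give 150, so two-sided 0.0125 is the plan's basis.

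**Step 2. Reproduce the enrolment target.** 203 / 0.65 = 312.3, so 313 per arm. 609 / 0.65 = 936.9, against the stated 938. 938 / 6 = 156.3, stated as 156 = 3 × 52. The gap between 936 and 938 is rounding and does not matter. So 52 is the number per arm per country.

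**Step 3. Power at the planned size.** 156 × 6 = 936; 936 / 3 × 0.65 = 202.8 evaluable per arm. Power = Φ(d√(n/2) − z₁) = Φ(0.375 × √101.4 − 2.498) = Φ(1.28) = 89.9%.

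**Step 4. Power with countries at the floor.** If all six halt at 52: 52 × 6 = 312 randomized, 104 per arm, 104 × 0.65 = 67.6 evaluable per arm. Power = Φ(0.375 × √33.8 − 2.498) = Φ(−0.318) = 37.5%, or 36.6% by t-test. With no attrition at all (104 per arm) it is 58%.

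Fewer countries at the floor, same formula:

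| Countries halting at 52 | Randomized | Evaluable per arm | Power |
|---|---|---|---|
| 0 | 936 | 202.8 | 90% |
| 1 | 832 | 180.3 | 86% |
| 2 | 728 | 157.7 | 80% |
| 6 | 312 | 67.6 | 37% to 38% |

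**Step 5. Baseline adjustment.** The primary model adjusts for the T0 value, which multiplies the SD by √(1 − r²). The article gives no correlation r, so these are assumptions: at 67.6 per arm, r = 0.3, 0.5 and 0.7 give power of 42%, 51% and 71%. All remain below 90%.

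**Step 6. Does inserting the words for per arm suffice?** Under simple randomization of 156 dyads, the SD of one arm's size is √(156 × 1/3 × 2/3) = 5.9, and its 95% range is about 41 to 64. If a country had to wait until its smallest arm reached 52, simulation gives a mean of about 175 dyads per country (95% range about 158 to 202), or about 1,047 in total against 936. The article does not say that countries wait in this way; the figures only show why a country total is the safer wording.

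**The case against.** A reader might infer that the plan tells each country to stop at 52 and that the trial is therefore set to run at about 37% power. The text does not support that. It says at least 52, which 156 also satisfies. The Recruitment section keeps screening open until the target population is reached and calls the numbers required by the power calculation realistic. Since 52 is exactly the per-arm number, an omission in the wording is the likeliest explanation. All of this stands. It makes 37% a worst case that needs all six countries to halt at the minimum, 35% attrition and no gain from baseline adjustment. It does not make the sentence right: a floor at one third of the requirement does not protect the target, and the Recruitment section gives no number to set against it.

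A reader might also infer that simple randomization is itself a fault to be replaced. The documents do not support this either. The power calculation needs 203 per arm across all countries, not equal arms within each country. With 936 dyads under simple randomization, simulated power averages 89.9% (95% range 88.3% to 91.3%), the same as with perfect balance. Within a country of 156, chance imbalance raises the standard error of a comparison by about 0.6% on average (95% range about −5% to +7%), and the by-country analyses are exploratory interaction tests.

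**Conclusion.** Wrong as written. The per-country number in the Allocation section contradicts the abstract and the Sample size calculation by a factor of three (52 against 156), most probably because the reference to arms was dropped. The stated design is otherwise sound: 203 per arm, 313 enrolled per arm and 90% power all reproduce.

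The size depends on how the sentence is acted on. If every country goes on to 156, nothing is lost. One country halting at the floor costs about 4 points of power (90% to 86%), and two cost about 10 (to 80%). All six halting gives about 37%, or 42% to 71% if baseline correlations of 0.3 to 0.7 are assumed. These figures rest on a two-sided alpha of 0.0125, an effect of 0.375 SD and 65% retention in every arm.

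**What to change.** Replace the Allocation sentence with one saying that recruitment within a country continues until 156 dyads (about 52 per arm) have been randomized, 936 in total. State it as a country total and not as a minimum for each arm, for the reason in step 6.

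The cost is one corrected sentence and a notice to the national teams. It adds no participants and leaves the design, the randomization service and the analysis unchanged. Blocked randomization stratified by country would bring each country closer to 52 per arm, but it is a design change that would need a formal amendment under the article's own rules. It is optional and separate from this correction.
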